**Fig. 1 Fig1:**
[figure not shown]
Recruitment and Procedure of the Study

### Interventions

In both dietary groups, weekly contacts with the dietician (via telephone or video calls) are scheduled to keep the participant and family motivated, respond to questions and assess adherence and nutritional quality. After 2 weeks, researchers contact the family to evaluate experiences with the diet so far. To keep track of daily changes in behavior, parents evaluate the severity of hyperactivity/impulsivity, attentional, physical and emotional problems on a 5-point scale (ranging from *1 no problems* to *5 severe problems*) every day (during the first 5 weeks and during the re-introduction phase of the ED). Dieticians discuss this daily assessment on the four subscales during their weekly contacts with parents. This daily assessment is specifically developed for the present study. To facilitate feasibility and adherence to the diet, parents receive examples of menus, recipes, shopping lists and advice for situations outside their home (e.g. parties).

#### Elimination diet

The goal of the Elimination Diet (ED) is to diminish symptoms of ADHD and emotion dysregulation symptoms by means of the exclusion of specific food components. The first part of the ED trajectory consists of a 5 week elimination phase where children follow a standardized ED supervised by a dietician (see Additional file 1: Appendix A). All known food allergens (proteins from milk, egg, wheat, fish (including shellfish and mollusks), soy, peanuts and nuts) and potential food triggers (gluten and histamine- releasing or histamine-containing products: see Additional file 1: Appendix A) will be eliminated. In addition, sugar intake is restricted in the elimination phase. Parents will receive a detailed list of products that children are allowed to eat during the elimination phase.

The second part (reintroduction phase) may last up to 12 months and consists of four phases (see Table 1; see Additional file 1: Appendix B). Every 14 days a new food is introduced according to a standardized scheme in a sufficient amount as to be able to trigger ADHD symptoms. In reintroduction phase one food allergens are reintroduced one by one to the standardized ED. If the reintroduction of a food allergen does not trigger recurrence of ADHD symptoms (based on the daily assessments of parents), this food allergen is added to the diet - after phase one is completed - and can be eaten again. If a food allergen does seem to trigger recurrence of ADHD symptoms (based on the daily assessments of parents), the food allergen is listed in the category ‘to be avoided’. In the next week, no new food allergen introduction takes place to allow the ADHD symptoms to decrease again to the level prior reintroduction. When ADHD symptoms have returned to the level prior reintroduction (based on the daily assessments of parents), another new food allergen is introduced in the week thereafter. Between phase one and two is a period of 2 weeks in which the standardized ED is followed, complemented with food allergens that did not trigger ADHD symptoms (‘Baseline diet +’). In the following phases sugar (phase two), histamine-releasing or histamine-containing products (phase three) and additives (phase four) are reintroduced. The procedures during reintroduction phases three and four are similar to reintroduction phase one. During phase two, accumulating amounts of sugar are added during 8 days. Despite the lack of consistent objective data demonstrating effects of sugar on cognition or behavior, subjective reports - by for example parents - of adverse effects of sugar are widespread [22, 23]. Therefore, we also assess whether sugar may trigger recurrence of ADHD symptoms.

**Table 1 Tab1:** Re-introduction Phase Elimination Diet

Phase	Period	Diet
*Elimination phase*	Weeks 1–5	Baseline ED
*Re-introduction phase*		
**Phase 1: allergens**	± 3 months	Baseline ED
Subsequently: proteins from milk, egg, wheat, fish, soy, peanuts, nuts		
	2 weeks	Baseline diet +
**Phase 2: sugar**	8 days	Baseline diet +
**Phase 3: histamine-releasing or histamine-containing products**	± 2.5 months	Baseline diet +
Subsequently: aromatic substances, specific foods, biogenic amine, nitrate, cocoa		
**Phase 4: additives**	± 2.5 months	Baseline diet +
Subsequently: sorbic acid, sulphites, glutamates/glutamic acid, artificial colorings and further examination (if needed) of products that child responded to by re-introducing products again		

During the reintroduction phase, parents have contact with a dietician every 2 months to identify foods that trigger ADHD symptoms in their child, to give mental support and to answer questions about the diet. In addition, depending on the parents’ needs, the researchers can provide mental support and advice to the parents via telephone. Furthermore, all foods and/or food components that have to be avoided are registered. Eventually this phase leads to a consolidated dietary advice about the specific foods to be avoided, while maintaining an otherwise normal diet. Participants who drop-out at any time can switch to CAU.

#### Healthy diet

The healthy diet aims to balance possible deficits in nutrient intakes or excessive intakes of nutrients, in order to reduce ADHD symptoms and emotion dysregulation symptoms (see Additional file 1: Appendix C). This diet is based on the Dutch dietary guidelines 2015 and the recommended daily consumption of food groups derived from those guidelines per sex and age group, as made by The Netherlands Nutrition Center (Table 2) [24, 25].

**Table 2 Tab2:** Recommended Daily Intake Food Groups

Food group	4–8 years Boys and girls	9–13 years Boys	9–13 years Girls
**Vegetables**	100–150 g 2–3 serving spoons	150–200 g 3–4 serving spoons	150–200 g 3–4 serving spoons
**Fruit**	1.5 pieces	2 pieces	2 pieces
**Bread, brown or whole-grain**	2–4 slices	5–6 slices	4–5 slices
**Grain products** (e.g. brown rice, whole-grain pasta) or potatoes	2–3 potatoes / serving spoons	4–5 potatoes / serving spoons	3–5 potatoes / serving spoons
**Dairy**	2 portions (300 ml)	3 portions (450 ml)	3 portions (450 ml)
**Cheese**	20 g 1 slice	20 g 1 slice	20 g 1 slice
**Meat, fish, chicken, eggs, vegetarian products, legumes** Variation is important!	Choose every week for example: -max. 250 g meat^a^ − 100 g fish − 2-3 eggs − 1-2 serving spoons legumes	Choose every week for example: -max. 500 g meat^a^ − 100 g fish − 2-3 eggs − 2 serving spoons legumes	Choose every week for example: -max. 500 g meat^a^ − 100 g fish − 2-3 eggs − 2 serving spoons legumes
**Nuts**	15 g	25 g	25 g
**Soft or liquid spreadable fats and cooking fats**	30 g^b^	45 g^b^	40 g^b^
**Fluid**	1–1.5 l	1–1.5 l	1–1.5 l

^a^*1 portion meat for 4–8 year olds = 50 g; for 9–13 year olds = 75 g*

^b^*5 g per slice; 15 g is 1 table spoon*

Consequently, some foods are allowed in unlimited quantities and frequencies (e.g. vegetables), others in restricted quantities and frequencies (e.g. honey), some in very restricted quantities and frequencies (e.g. processed meat) and some foods are not allowed (e.g. white bread) (see Additional file 1: Appendix C). Parents receive this detailed list of which foods are allowed in which quantity and frequency (see Additional file 1: Appendix C). This healthy diet is prescribed in a strict and structured manner (e.g. stressing the importance of adhering to the diet), making the diet comparable to ED regarding impact to the family, household structure and attention towards the child. It is not the intention to affect the allergen content of the diet or losing or gaining weight.

Contact frequency with a dietician and researchers is similar to the ED. The second phase of the healthy diet consists of two-monthly supervising by a dietician. During these supervisions, adhering to the diet and the ADHD symptoms and emotion dysregulation symptoms are evaluated (see Additional file 1: Appendix D).

#### Care as usual (CAU)

According to the Dutch Multidisciplinary guidelines for the diagnosis and treatment of ADHD [26] and authoritative international guidelines [27], CAU for elementary school–aged children (5–12 years of age) with ADHD consists of the prescription of medication approved for ADHD and/or evidence-based parent and/or teacher-administered behavior therapy, preferably both medication and behavior therapy. First-line option for medication is methylphenidate, second-line option is lisdexamfetamine or dexamfetamine, and third-line options atomoxetine or guanfacine [27]. The school environment is part of the treatment plan by instructing teachers how to (a) best modify the classroom environment to minimize distractions for the child and (b) give teaching instruction to the child with maximum learning efficiency.

### Outcomes

Outcome parameters will be assessed as shown in Table 3.

**Table 3 Tab3:** Outcome Parameters from Baseline to 12 Months after Baseline

Measurement	Time^**a**^	Instrument
**Descriptives**		
Prior beliefs	T0, T1	5-item questionnaire
IQ	T0	WPPSI-III or WISC-III
Demographics	T0	Separate questions
Parental psychopathology	T0, T2, T3	GHQ
Parental ADHD symptoms	T0	ADHD Rating Scale
**Primary outcome**		
Respondership	T1, T4	SWAN, SDQ
**Secondary outcomes**		
Blinded ADHD assessment	T0, T1, T4	DB-DOS
Parent & teacher comorbidity ratings	T0, T1, T4	SDQ, CSBQ, BRIEF, UPPS-P, EDI
Cognitive performance	T0, T1, T4	COTAPP
School performance	T0, T4	Monitoring system Dutch education
Motor activity and sleep pattern	T0, T1, T4	Actigraph
Physical measurements	T0, T1, T4	Weight, height, blood pressure, heart rate
Somatic complaints	T0, T1, T2, T3, T4	Pittsburgh side-effects rating scale
Sleep problems	T0, T1, T2, T3, T4	5-item questionnaire
Quality of life	T0, T1, T2, T3, T4	EQ-5D
Food consumption & eating habits	T0	Questionnaire dietary pattern
	T0, T4	Nutritional assessment (‘Eetmeter’)
Nutritional quality	T0, T2, T3, T4	Nutritional assessment (‘Eetmeter’)^b^
	T0, T1, T2, T3, T4	Expert view
	T0, T1, T4	Blood sample
Carer-related quality of life	T0, T1, T2, T3, T4	CarerQol, PSQ
Parenting styles and family functioning	T0, T1, T4	FFQ, BSBP
Adherence	T1, T4	Morisky Adherence Scale, food diary, separate questions
Satisfaction	T1, T4	GGZ-Thermometer
Cost measurements	T1, T2, T3, T4	Tic-P

*WPPSS-III* Wechsler Preschool and Primary Scale of Intelligence, *WISC-III* Wechsler Intelligence Scale for Children, *GHQ* General Health Questionnaire, *SWAN* Strengths and Weaknesses of ADHD-symptoms and Normal-behaviors (SWAN) rating scale, *SDQ* Strength and Difficulties Questionnaire, *DB-DOS* Disruptive Behavior Diagnostic Observation Schedule, *CSBQ* Children’s Social Behavior Questionnaire, *BRIEF* Behavior Rating Inventory of Executive Function, *UPPS-P* Urgency, Premeditation, Perseverance, Sensation seeking, and Positive urgency Impulsivity scale, *EDI* Emotion Dysregulation Inventory, *COTAPP* Cognitive Task Application, *PSQ* Parenting Stress Questionnaire, *EQ-5D* EuroQol Five Dimensions Health Questionnaire, *FFQ* Family Functioning Questionnaire, *BSBP* Brief Scale of Parental Behavior, *Tic-P* Trimbos and iMTA questionnaire on Costs associated with Psychiatric illness’

^a^T0 baseline; T1 five weeks after baseline; T2 four months after baseline; T3 eight months after baseline; T4 12 months after baseline. ^b^ Only parents of healthy diet participants who continue the diet after five weeks, register food consumption at T2 and T3

#### Primary outcome

##### Respondership

Parents and teachers are invited to rate the child’s ADHD traits using the SWAN questionnaire. The SWAN consists of 18 DSM-IV-based items scored on a 7-point Likert scale ranging from 3 (*far below average*) to -3 (*far above average*) with higher scores reflecting more severe ADHD symptoms [21]. Items 1 to 9 assess symptoms of the ADHD inattentive type and items 10 to 18 assess symptoms of the ADHD hyperactive/impulsive type. The Dutch version of the SWAN questionnaire is a reliable instrument (Cronbach’s α = .87) [28, 29] and demonstrates adequate convergent and discriminant validity [28, 29]. Parents and teachers also are asked to fill out the Strengths and Difficulties Questionnaire (SDQ) to assess emotion dysregulation [30]. The SDQ Dysregulation Profile (SDQ-DP) includes fifteen items representing emotional symptoms, conduct problems and hyperactivity-inattention [31]. The items can be answered on a 3-point scale ranging from 0 (*not true*) to 2 (*definitely true*) with higher scores indicating more emotion dysregulation problems. The Dutch version of the SDQ-DP demonstrates adequate reliability (Cronbach’s α = .85) and construct and longitudinal validity [31].

To align with the evaluation of the diet after 5 weeks, response to treatment will be evaluated by assessing the change in ADHD and emotion dysregulation symptoms at T0 and T1 or T4 (i.e. SWAN inattentive scale, SWAN hyperactive/impulsive scale and SDQ dysregulation profile rated by both parent and teacher: together six scales) [32]. A 30% or more symptom decrease will be regarded as a significant response to treatment (i.e. positive value), and a 30% or more symptom increase is regarded as significant deterioration of symptoms (i.e. negative value) [9, 33]. The primary outcome variable ‘respondership’ is divided into five categories:
Full responder (significant response on both parent and teacher rated scales): all scales are ≥ − 20% AND at least one of three parent rated scales shows a ≥ 30% symptom reduction AND at least one of three teacher rated scales shows a ≥ 30% symptom reduction.Partial responder (significant response on parent or teacher rated scale):
All scales are > − 30% AND at least one of three parent rated scales shows a ≥ 30% symptom reduction AND all three teacher rated scales are < 30%.OR: All scales are > − 30% AND at least one of three teacher rated scales shows a ≥ 30% symptom reduction AND all three parent rated scales are < 30%.OR: All scales are > − 30% AND at least one of three parent rated scales shows a symptom reduction between 20% & 30% AND at least one of three teacher rated scales shows a symptom reduction between 20% & 30%Mixed responder (significant response on at least one parent rated scale and significant deterioration on at least one teacher rated scale or vice versa):
At least one of three parent rated scales shows a ≥ 30% symptom reduction AND at least one of three teacher rated scales shows a ≤ − 30% symptom deterioration.OR: At least one of three teacher rated scales shows a ≥ 30% symptom reduction AND at least one of three parent rated scales shows a ≤ − 30% symptom deterioration.Non-responder (no significant response): all six scales are > − 30 and < 30%.Deterioration (significant deterioration on at least one parent or teacher rated scale): all scales are < 30% AND at least one of three parent rated scales shows a ≤ − 30% symptom deterioration OR at least one of three teacher rated scales shows a ≤ − 30% symptom deterioration.

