One of the inclusion criteria includes an ADHD diagnosis. To confirm this diagnosis, children are screened by the researchers via a structured psychiatric interview with the parents based on the DSM-IV (Kiddie Schedule for Affective Disorders and Schizophrenia: K-SADS) [20]. The ADHD section and the ODD section of this interview are used. The latter is used to check for comorbidities. Also, teachers fill out the Strengths and Weaknesses of ADHD-symptoms and Normal-behaviors (SWAN) rating scale [21]. To confirm the clinical ADHD diagnosis, there should be a minimum of six out of nine symptoms present in at least one domain (i.e. hyperactivity/impulsivity or inattentiveness), based on parent and teacher ratings. Parents and teachers have to separately rate at least four out of nine symptoms in one domain. Children are not able to participate if this criterion is not met.

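### Respondership rests on a 20%/30% change from baseline, but four of its six scales are SWAN scores that run through zero, where percent change can be undefined, reversed or unstable

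*Protocol article*

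**What the plan says.** All of the following is in the Protocol article.

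- **Coding (Respondership).** SWAN items are "scored on a 7-point Likert scale ranging from 3 (*far below average*) to -3 (*far above average", "with higher scores reflecting more severe ADHD symptoms". Items 1 to 9 form the inattentive scale and items 10 to 18 the hyperactive/impulsive scale.
- **Rule (Respondership).** "A 30% or more symptom decrease will be regarded as a significant response to treatment (i.e. positive value"), while "a 30% or more symptom increase is regarded as significant deterioration of symptoms (i.e. negative value"). A 20% cut-off is also used in the full and partial responder definitions.
- **Scales (Respondership).** Two SWAN scales and the SDQ dysregulation profile, "rated by both parent and teacher: together six scales". Four of the six are SWAN.
- **Categories (Respondership).** Full, partial, non-responder and deterioration each carry a condition on every scale, for example "Non-responder (no significant response): all six scales are" between the two 30% limits. Only mixed has no such condition. It needs a response from one rater and a deterioration from the other.
- **SDQ items (Respondership).** "The items can be answered on a 3-point scale ranging from 0 (*not true*) to 2 (*definitely true"), so the 15-item profile runs from 0 to 30 and cannot be negative.
- **Entry (Participants).** Any ADHD presentation is admitted, and "there should be a minimum of six out of nine symptoms present in at least one domain". Each rater must endorse at least four of nine symptoms in one domain.

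The article gives no recoding of the SWAN and no rule for a zero, negative or near-zero T0 score.

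**The concern.** A percent change has a stable meaning only on a score with a meaningful zero and positive baselines. Here zero means average behaviour, and half the range lies below it. The 30% threshold is therefore tied to an arbitrary origin, and for some baselines the computed change contradicts what happened to the child.

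Respondership carries the primary objective and the ordinal regression (Statistical analyses). Responder percentages also feed the interim review (Data monitoring), and the category determines what families are told after five weeks (Study design, 2nd phase). Labels produced by the arithmetic rather than by symptom change would fall on both diet arms and add misclassification to the main comparison.

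**Working it through.** **The plan's own figure.** The stated power (0.99 and 0.64, 81 per arm, Sample size and power) reproduces from Table 4: 0.991 and 0.644 by simulating the proportional-odds score test. It takes the category frequencies as given and does not depend on SWAN coding.

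**Step 1: behaviour of the rule.** Change = 100 × (T0 − T1)/T0, positive for improvement, as the article defines it. Recoding items 0-6 adds 9 × 3 = 27 to the sum.

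| T0 to T1 (sum) | True direction | As coded, -3 to 3 | Items recoded 0-6 |
|---|---|---|---|
| 18 to 12 | better | 6/18 = +33% | 6/45 = +13% |
| 3 to 2 | better by one point | 1/3 = +33% | 1/30 = +3% |
| 0 to -5 | better | undefined | 5/27 = +19% |
| -3 to -6 | better | 3/(-3) = -100% | 3/24 = +13% |
| -3 to -1 | worse | (-2)/(-3) = +67% | (-2)/24 = -8% |

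Dividing by the absolute value of T0 would repair the sign but not the zero and near-zero cases. The first row shows that the meaning of 30% depends on the origin even where the sign is right.

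**Step 2: can such baselines occur?** The domain that does not qualify the child has no floor. Even the qualifying domain can be non-positive. If a symptom is an item rated +1 or more (assumption; the article does not define it), a rater giving four items +1 and five items -1 meets the per-rater minimum with a sum of 4 − 5 = -1.

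**Step 3: effect of one scale on the category.** Take a child with a 30% reduction on one parent and one teacher scale, no change on three others, and one parent SWAN scale going from -3 to -6. That scale reads -100%, so the all-scales conditions for full and partial response fail. A teacher response with a parent deterioration then makes the child mixed instead of full. A child with five unchanged scales and the same sixth scale becomes deterioration instead of non-responder. If a scale is undefined, the four categories with an all-scales condition cannot strictly be assigned.

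**Step 4: how many children?** The documents give no SWAN mean, SD or retest correlation, so these are assumptions. With mean item score m and between-child SD s, sums rounded to whole points and scales independent, p = Φ((0.056 − m)/s), where 0.056 = 0.5/9. For two domains and two raters, the share with at least one non-positive scale is 1 − [(1 − p1)(1 − p2)]².

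- One domain elevated (means 1.5 and 0.3). SD 0.6: p = 0.008 and 0.342, so 1 − (0.992 × 0.658)² = 57%. SD 0.9: p = 0.054 and 0.393, so 1 − (0.946 × 0.607)² = 67%.
- Both elevated. Means 1.8 and 1.5, SD 0.6: p = 0.002 and 0.008, giving 2%. Means 1.5 and 1.5, SD 0.9: p = 0.054 for each, giving 1 − 0.946⁴ = 20%.

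A separate item-level simulation applied the entry rule (latent item mean 0.5-2.0, scale and item SD 0.9, symptom at +1 or +2). About 2-42% of eligible children had a non-positive SWAN scale, and about 4-37% had one at 1-3 points.

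**Step 5: labels with no true change.** Two ratings were simulated with retest correlation 0.7-0.9, SD 0.6-0.9, SDQ profile mean 12 and SD 5. The entry rule was not applied, and an undefined scale counted as neither response nor deterioration.

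| Children | Mixed, as coded | Mixed, 0-6 coding |
|---|---|---|
| One domain elevated | 29-65% | 2-16% |
| Both domains elevated | 8-54% | 2-11% |

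The two columns are not like for like. At T0 = 18, a 30% change is 5.4 points as coded and 13.5 points on 0-6 coding, so part of the gap is a stricter threshold.

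**The case against.** The article condenses a fuller protocol, and a recoding may be stated there. That defence is weak. The article is not silent: it gives the signed coding and the percent rule together, with detailed cut-offs, and the two cannot be applied together to every child.

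Other points stand. The two SDQ scales cannot change sign; only a zero baseline is a problem there. SWAN scales with clearly positive baselines give the right direction. ANCOVA at T1 with T0 as covariate is already planned for continuous outcomes. The stated power is not contradicted.

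A reader might infer three stronger things, and the documents support none of them:

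- **That most children are affected.** The 67% figure belongs to children with one elevated domain at SD 0.9. The article admits any presentation and states no mix.
- **That one faulty scale decides the category by itself.** Mixed needs opposite results from the two raters, so one scale cannot create it alone. It can block or change a category.
- **That the primary endpoint is largely noise, or that the diet contrast shrinks by a known amount.** No treatment effect was simulated under either coding.

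**Conclusion.** The concern holds. As written, the rule is wrong for part of the possible baseline range, which is more than missing detail. Four of the six scales behind the primary outcome can be undefined, reversed or moved past 30% by a single point, and the entry criteria make such baselines foreseeable. This needs no assumption.

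The extent does need assumptions. The share with a non-positive SWAN scale at T0 is about 2-20% if both domains are elevated and 57-67% if one is. Without any true change, about 8-54% and 29-65% respectively would be labelled mixed, against about 2-16% with 0-6 coding. These figures show that the problem could be material; they do not estimate this trial. The rule should be corrected before the primary analysis.

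**What to change.** Before outcome data are analysed:

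1. Compute change on a SWAN score with a fixed non-negative origin, for example a unipolar severity score with average or better rated 0 and the symptom side 1 to 3, giving 0-27 per scale.
2. Confirm what the 20% and 30% cut-offs mean on that score. They do not carry over automatically.
3. Fix how a SWAN scale with zero or near-zero T0 is handled, because a unipolar score can still be zero. Any minimum T0 must fit the entry rule, so that an eligible child keeps at least one SWAN scale per rater. A floor of 9 of 27 would fail this: four symptoms at +1 with the rest average or better score 4, and six score 6. A low-baseline scale must still be able to register worsening. A similar floor for the SDQ profile is a matter of choice, since that score cannot change sign.
4. Designate the planned T1 ANCOVA on the untransformed SWAN and SDQ profile scores as the supportive analysis of the primary question.

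The cost is analysis wording and re-deriving one variable from item data that the trial collects anyway. There are two drawbacks: the analysed category may differ from the one already reported to a family, and the recoding changes what a 30% change means, which the report should state.

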### Statistical analyses

All primary analyses will be Intention To Treat. The primary outcome will be measured as an ordinal variable with five categories. Therefore, the effect of the intervention will be measured in terms of odds ratio, comparing odds for reducing ADHD symptoms and emotion dysregulation symptoms in the elimination diet group with the corresponding odds in the healthy diet group. Multiple logistic regression analyses will performed to compute the odds ratio and 95% confidence intervals, using ordinal logistic regression analysis. The CAU group will be used as a reference group.

Differences in continuous outcome measures between the dietary trajectories will be determined with analyses of ANCOVA. The follow-up value (T1, after five weeks) will be added as the dependent variable and the baseline value will be added as covariate. The two dietary groups will be compared on all outcomes at T1, using T0 scores as covariates. Clinical significance will be estimated using the partial eta squared effect. The CAU group will be used as a reference group.

In addition, a repeated measures ANOVA will be performed. First, the whole sample will be used (Intention to Treat) to determine whether adding a dietary treatment has beneficial outcomes on costs and effects of the whole treatment trajectory after 12 months (regardless of continuing the dietary treatment after 5 weeks or not). Next, per-protocol and post-hoc analyses will be performed using repeated measures ANOVA where the main outcome measures will be compared across the three conditions (i.e. elimination diet; healthy diet; CAU). Also, we will determine how many children adhered to the diet after 12 months, whether the intervention effects maintained after 12 months, which products are eliminated from the diet after 12 months and the nutritional quality of the attained diet after 12 months.

Finally, two moderator analyses will be performed: one comparing dietary responders versus non-responders (predicting respondership) and another comparing children/families adhering to a dietary treatment versus children/families that are not able to do so (predicting adherence). Both moderator analyses will be performed to compare children/families after 5 weeks and after 1 year of treatment.

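### The five respondership categories overlap in two places and leave two patterns unclassified, so the ordinal primary outcome is not fully defined

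*Protocol article*

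**What the plan says.** The Statistical analyses section states: "The primary outcome will be measured as an ordinal variable with five categories". Each child therefore needs exactly one value. The Respondership section supplies the rules, using six scales (three rated by the parent, three by the teacher) and one threshold: a "30% or more symptom decrease will be regarded as a significant response to treatment". A rise of 30% or more counts as deterioration.

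In summary, with positive numbers meaning improvement:

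- **Full.** The rule opens "Full responder (significant response on both parent and teacher rated scales): all scales are" at or above -20%. It also needs at least one parent scale and one teacher scale at 30% or more.
- **Partial.** Every scale must be above -30%. Routes 1 and 2 need one informant at 30% or more and the other informant wholly below it, for example "AND all three teacher rated scales are < 30" per cent. Route 3 needs that "at least one of three parent rated scales shows a symptom reduction between 20% & 30" per cent and that "at least one of three teacher rated scales shows a symptom reduction between 20% & 30" per cent.
- **Mixed.** Response from one informant and deterioration from the other.
- **Non-responder.** "Non-responder (no significant response): all six scales are" strictly between -30% and 30%.
- **Deterioration.** "Deterioration (significant deterioration on at least one parent or teacher rated scale): all scales are" below 30%, AND a parent scale at or below -30% OR a teacher scale at or below -30%, without brackets.

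No order of precedence is given. The section on the second study phase uses the same categories to decide who is invited to continue the diet and who is advised to stop.

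**The concern.** An ordinal regression needs categories that exclude each other and cover every case. The article states its algorithm in full, so this is not detail left to an analysis plan: the stated rule gives some children two categories and others none.

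Partial and Non-responder lie two steps apart on the ordinal scale, so that overlap is not a neighbouring-category nuance. Route 3 also admits children with no scale at the 30% that the text calls a significant response, which sits badly with Partial's own label. Full responders matter because the Sample size and power section defines the clinically relevant effect as twice as many of them on the elimination diet as on the healthy diet. Researchers know the allocation, so unwritten coding choices would not be made blind.

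**Working it through.** **The plan's own figure.** The article gives no share of unclassifiable children. Its only related figure is power with 81 per arm and two-sided 0.05: 0.99 in scenario 1 and 0.64 in scenario 2. The proportional-odds score test (tie-corrected Wilcoxon), run on 200,000 multinomial draws from the Table 4 counts, gives 0.994 and 0.648. Scenario 2 varies with method: 0.619 from the percentages, 0.70 from a fitted ordinal logit (500 replicates) and 0.54 from the Whitehead formula. The stated power is reproduced. It presumes that each child falls in one cell.

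**Example children** (unlisted scales at 0):

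| Parent | Teacher | Categories met |
|---|---|---|
| +25 | +25 | Partial (route 3) and Non-responder |
| +35, +25 | +35, +25 | Full and Partial (route 3) |
| +35, -25 | +35 | none |
| +35, -35 | all 0 | none |

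In the third row the -25 fails the floor for Full, routes 1 and 2 fail because both informants reach 30%, and route 3 has no scale in its band. In the fourth row Mixed needs the other informant to deteriorate, Partial needs all scales above -30%, and Deterioration needs all scales below 30%.

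**These are the only gaps.** Take Deterioration as *all below 30% AND (parent or teacher at or below -30%)*.

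1. No scale at 30% or more: Non-responder or Deterioration always applies.
2. One informant at 30% or more: Partial if every scale is above -30%; Mixed if the other informant is at or below -30%; otherwise only the same informant deteriorates, which is a gap.
3. Both informants at 30% or more: Full if the worst scale is at least -20%; Mixed if it is at or below -30%; in between, only route 3 can apply, so without 20-30% scales from both informants there is a gap.

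**Count on a grid.** Let each scale take -40, -25, 0, 25 or 40, giving 5^6 = 15,625 patterns.

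- Same-informant conflict: triples containing both 40 and -40 number 125 - 2×64 + 27 = 24. The other informant has 3^3 = 27 patterns. Total 2 × 24 × 27 = 1,296.
- Worst scale at -25 with both informants responding: (64 - 27)^2 - (27 - 8)^2 = 1,369 - 361 = 1,008. Route 3 catches 18^2 - 12^2 = 180 of these. Total 828.
- No category: 1,296 + 828 = 2,124.
- Partial and Non-responder: (27 - 8)^2 = 361. Full and Partial: 12^2 = 144. Two categories: 361 + 144 = 505.

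These are pattern counts, not probabilities.

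**The unbracketed reading.** Read as *(all below 30% AND parent at or below -30%) OR teacher at or below -30%*, Deterioration absorbs the teacher version of the same-informant gap (24 × 27 = 648 patterns, leaving 2,124 - 648 = 1,476). The parent version stays unplaced. A child with parent +35 and teacher -35 becomes both Mixed and Deterioration.

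**Share of children (assumed inputs).** Six correlated normal changes were simulated over 100 settings of 100,000 children each: mean improvement 0-30%, SD 15-40 points, correlation 0.5-0.8 within and 0.1-0.5 between informants. None of these values is in the article.

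| Problem | Range | Median |
|---|---|---|
| Zero or two categories | 2.4-17.5% | 7.8% |
| No category | 0-6.4% | 0.2% |
| Partial and Non-responder | 0.4-8.7% | 2.5% |
| Full and Partial | 0.1-13.8% | 3.3% |

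Of 162 randomized children, 2.4% is about 4 (0.024 × 162 = 3.9), 7.8% about 13 (12.6) and 17.5% about 28 (28.4). Settings tuned towards the Table 4 margins gave about 3% to 12%. With all six scales independent the total was 12% to 15%, of which gaps were 8.6% to 9.8%.

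**The case against.** Much of the ambiguity can be settled from the text's own labels. Full is described as response from both informants and Partial as response from one or the other, so a child who meets every Full condition is naturally Full. Route 3 would have almost no function unless it overrode Non-responder. The Deterioration label joins the two informants by OR, which supports the bracketed reading. Taking the categories in listed order then leaves only the gaps. In simulations with mean improvement 20% and 10% in the two arms, opposite resolutions of the overlaps changed power by no more than about 2 points (0.965 to 0.956 at SD 20; 0.746 to 0.730 at SD 30).

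This stands as an argument about size. It does not remove the defect: the order is nowhere stated, the Partial label conflicts with letting route 3 override Non-responder, and no precedence rule fills the gaps.

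Stronger readings are tempting and not supported:

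- A reader might infer that about one child in ten lacks a single value. Those simulations, with SD 20-30 and correlations 0.5 and 0.3, do give 9-11%. They also give 35-40% full responders on the elimination diet, against 15-20% in Table 4, and the article gives no distribution to choose by.
- A reader might infer that Full versus Partial is the contrast the plan calls clinically relevant. That contrast is the number of full responders between the two diets.
- A reader might infer that the categories will be settled after the data are seen. Because they are applied to each child at five weeks, some working rule is presumably in use, although the article does not show it.

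**Conclusion.** The definition of the primary outcome is wrong as written. The categories are neither mutually exclusive nor exhaustive, and this follows from the wording alone. There are two overlaps (Partial with Non-responder, Full with Partial), two gaps (worst scale between -20% and -30% with both informants responding; response and deterioration from the same informant), and one AND/OR that needs brackets.

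The share of children affected cannot be derived from the article. Under the assumed normal changes it is about 2% to 18%, with gaps of 0% to 6%, or somewhat more if the six scales were independent. In the typical setting most of the total is overlap; where changes vary widely the gaps can be the larger part. The stated power is not in error.

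**What to change.** Before outcome data are examined by arm, fix one ordered, exclusive and exhaustive derivation for the analysis variable:

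1. Bracket Deterioration as *all scales below 30% AND (a parent scale at or below -30% OR a teacher scale at or below -30%)*.
2. State that Full takes precedence over Partial.
3. State whether the 20-30% route takes precedence over Non-responder and, if it does, exclude those children from Non-responder.
4. Assign the two gap patterns to named categories. For example, both informants responding with a worst scale between -20% and -30% could go to Partial, and same-informant conflict to Mixed. The latter widens Mixed beyond its cross-informant definition and should be declared as such.
5. Report a sensitivity analysis with the alternative placements.

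The section on the second study phase bases advice on continuing or stopping the diet on the same categories, so it and the Respondership section must be reconciled. No clinical rule is proposed here.

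The cost is one paragraph of wording, one re-derived variable and one sensitivity table. The downside is that a few children may carry an analysis category that differs from the one used for their advice at T1; their number should be reported.
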